### Intervention and control condition

Participants randomised to the intervention arm will get access to an mHealth app aimed at lifestyle behavioural change, supported by a coach. This interactive app facilitates self-management of dementia risk factors (hypertension, dyslipidaemia, active smoking, overweight, lack of physical exercise and unhealthy diet). The participants will be supported by an experienced lifestyle coach trained in motivational interviewing, who will be matched to the ethnicity of the participants with one of the coaches able to speak Turkish for Turkish participants. The coaches will assist participants in formulating simple, measurable, achievable, realistic and time-bound (SMART) goals and support them in achieving these goals. Their role is to guide them in their lifestyle change. They are instructed to recommend participants with medical questions to seek help from their doctor. Also, mental health-related questions are beyond the scope of our intervention, and will result in a recommendation to visit their doctor. Participants can contact the coach via the app through chat, and coaches will be motivated to stay in contact with the participants at least once a month. After secure login, the app shows the participants’ dementia risk profile, based on baseline assessment. Participants can set goals for lifestyle change, monitor these goals and enter self-measurements, for example, weight, blood pressure and physical exercise. Progress over time is visually presented whenever feasible. Additionally, the app contains evidence-based education modules, including educational videos specifically designed for this study population, featuring the health coaches. The intervention app will be available in three versions for each ethnicity, with culturally acceptable content. The two versions for the Dutch and South-Asian Surinamese population will be available in Dutch; the version for the Turkish population will be available in both Dutch and Turkish. Those randomised to the control condition will have access to an app which is similar in appearance, but lacks the interactive features of coach-support and monitoring risk factors. Participants are informed that there are two versions of the app and that they will be randomly assigned to one. They are not made aware that one app serves as the active intervention while the other represents the control condition. The control app provides only static information about healthy lifestyles, without incorporating culturally specific content, and is available in both Dutch and Turkish.

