### Study procedures

The study procedures are visualised in figure 2. Potentially eligible participants, based on information from the HELIUS study, will be invited via a letter in Dutch and Turkish to participate in the MIND-PRO study starting from July 2024 and ending in July 2026. The planned recruitment period is 12 months. We expect to be finished with recruitment in July 2025. A second invitation mail or email will be sent to those who did not respond to the first invitation. When there is still no response, we will call the potentially eligible participants to ask whether they want to participate. Those who are willing to participate will undergo a prescreening call to assess their eligibility for a further screening visit and subsequent baseline visit. During the screening visit, written informed consent will be obtained and additional measurements (weight, blood pressure, non-HDL cholesterol and assessment of cognitive functioning) will be conducted. Also, data on medication (antihypertensives, cholesterol-lowering drugs, diabetes treatments and antidepressants) will be collected. At the end of the screening visit, the MIND-PRO app will be downloaded with an explanation how to fill in the self-assessment questionnaires in the app. Participants will be asked to fill out the questionnaires themselves in the app. After the screening visit, the baseline visit will take place during which the self-assessment questionnaires will be checked and completed and the participant will be randomised to the intervention or control group, stratified by ethnicity. Six months after randomisation, participants will be requested to fill out a questionnaire on adverse events, which will be sent via the app. They will also be asked about their healthcare utilisation, specifically general practitioner visits, dietitian or physiotherapist visits and hospital visits. Additionally, all participants in the intervention group will be asked to fill out a questionnaire on implementation outcomes in the app 6 months after randomisation. Those who do not fill out the questionnaires will be called and the questionnaires will be administered by an assessor by telephone. For a more in-depth, qualitative assessment of implementation outcomes, a purposive sample from the intervention group of approximately 30 participants (10 from each ethnic group) will be asked to participate in an interview (table 2). At the end of the study, the questionnaires, medication use, healthcare utilisation and measurements performed during the screening visit will be repeated. Assessors will be matched to the participants’ ethnicity as much as possible.

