### Randomisation and blinding

Randomisation will take place in the app using a computer algorithm in a 1:1 manner, stratified by ethnicity. Randomisation will be carried out by trained assessors at the baseline visit. Participants will be informed that they are randomised to one of two different smartphone apps that can provide support in changing their lifestyle to reduce the risk of dementia. Partners or first-degree family members who also participate in the MIND-PRO study will automatically be allocated to the same treatment arm to limit contamination. Outcome assessment will be performed by an assessor who is blinded to treatment allocation. The coaches who support participants in behaviour change are, due to the nature of the intervention, not blinded. A certain level of unblinding during outcome assessment is conceivable, since a participant could share details about participation in the MIND-PRO app specifically to the outcome assessor. Participants and assessors are therefore instructed to not discuss the intervention with each other. If any unblinding occurs, its impact is likely limited since our primary outcome consists solely of objectively measured parameters.

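### A relative who joins after a family member has been randomised has an allocation that is fixed, and could be discovered, before consent and the eligibility check

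*Protocol article*

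**What the plan says.** Allocation is individual: "Randomisation will take place in the app using a computer algorithm in a 1:1 manner, stratified by ethnicity". The Randomisation and blinding section then adds the family rule, that partners or first-degree relatives who also take part "will automatically be allocated to the same treatment arm to limit contamination". It also says who acts and when: "Randomisation will be carried out by trained assessors at the baseline visit".

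Study procedures gives the order for each person: an invitation, a prescreening call, a screening visit, then a baseline visit. Consent and the physical measurements come first ("During the screening visit, written informed consent will be obtained and additional measurements"). At the later baseline visit "the participant will be randomised to the intervention or control group, stratified by ethnicity". On the time available, it says: "The planned recruitment period is 12 months".

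The Intervention and control condition section describes a control app of similar appearance with no coach and no risk-factor monitoring. Of participants it says: "They are not made aware that one app serves as the active intervention while the other represents the control condition".

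The article does not say that family members must be identified or screened together before the first of them is randomised. Nor does it treat later-entering relatives separately in the analysis.

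**The concern.** For someone with no relative in the trial the sequence is sound: consent, eligibility and physical measurements are complete before the allocation exists. For a relative who enters after a family member has been randomised, the order is reversed. That person's allocation follows with certainty from the first member's, and it exists before the relative has agreed, been judged eligible or been measured.

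Two decisions could then depend on the arm. One is the relative's own acceptance, if he or she has seen the app at home. The other is the eligibility judgement, since Box 1 excludes people with any condition thought likely to limit compliance or follow-up over the year. If either differs by arm, the late joiners in the two arms are not comparable. Adjusting for measured covariates would not reliably repair that, because motivation is not among them. In addition, the primary outcome is change from baseline, and a late joiner's baseline may be taken after some exposure to the relative's app.

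**Working it through.** **Does the text allow the problem?**

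1. The same-arm rule is deterministic (Randomisation and blinding).
2. Consent, screening and randomisation are per person, within a 12-month recruitment period (Study procedures). Staggered entry within a family is therefore permitted, though not described.
3. The arm labels are withheld, but the presence of a coach and of monitoring is visible to anyone who sees the app in use (Intervention and control condition). The arm is thus discoverable. The article does not say that it is disclosed.
4. The remarks on blinding cover other matters. The Randomisation and blinding section argues that unblinding at outcome assessment matters little because the outcomes are objective, which concerns measurement. The Discussion treats close-knit communities as a source of contamination, and selection as a question of generalisability. None of these addresses who enters each arm.

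**The plan's own figure.** From the Sample size section: difference 0.107, SD 0.454, alpha 0.05, power 80%. Taking alpha as two-sided,

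n per arm = 2 × (1.960 + 0.842)² × 0.454² / 0.107² ≈ 283,

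against 277 stated. Power at 277 per arm is 0.792. The total is 554 / 0.80 = 692.5, against 692 stated. The plan's figure reproduces closely, and this point does not change it.

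**Size of a possible bias (illustration; both inputs are assumptions).** Let f be the share of each arm made up of late-joining relatives, and s the difference between arms in their mean change that arises from selection alone. Then

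bias in the overall contrast = f × s.

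The shifts shown are 0.05, 0.107 (the whole target difference) and 0.227 (half of 0.454). Each cell gives the bias and its percentage of 0.107.

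| f | people of 692 | s = 0.05 | s = 0.107 | s = 0.227 |
|---|---|---|---|---|
| 2% | 14 | 0.001 (1%) | 0.002 (2%) | 0.005 (4%) |
| 5% | 35 | 0.003 (2%) | 0.005 (5%) | 0.011 (11%) |
| 10% | 69 | 0.005 (5%) | 0.011 (10%) | 0.023 (21%) |

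For scale, the standard error of the contrast at 277 per arm is 0.454 × √(2/277) = 0.0386. The middle column runs from 0.0021/0.0386 = 0.06 to 0.0107/0.0386 = 0.28 of a standard error.

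The sign is not determined. More motivated joiners in the coached arm would inflate the effect. Exposure to the coached app before a late joiner's baseline would shrink it.

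**The case against.** The strongest reply is that this reads much into a condensed article. The order in which family members are identified and enrolled is an operational matter that the full protocol may settle, and the flow chart in Figure 2 was not available in the text reviewed. The rule also has a good purpose: splitting families between arms would bring back the contamination it is meant to prevent. Both arguments stand. They support keeping the rule, but they do not supply concealment for relatives who enter late under the rule as written.

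Several stronger readings are tempting and are not supported:

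- **That late relatives, or the assessors screening them, know the arm.** The article does not say so. Labels are withheld, the apps look alike and the allocation runs in the app. The arm is fixed and discoverable; that it is known is not shown.
- **That a coached participant draws motivated relatives into the trial.** Entry is by invitation, mainly from the HELIUS database, with primary care practices as a reserve. No family referral is described. Being invited does not depend on a relative's arm; only acceptance and the eligibility judgement could. The age range of 50-75 years also limits the eligible pairs, mostly to partners and siblings.
- **That retention differing by arm is part of the problem.** It can affect every participant and does not follow from the family rule.
- **That the bias is large.** One can reach 0.15 × 0.2 = 0.03, or 28% of the target. That needs 15% of the intervention arm (about 52 of 346) to be late-joining relatives with no control counterpart. It also needs their change to be 0.2 better regardless of the intervention, nearly twice the effect the trial is powered to detect. Nothing in the article supports those inputs.

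**Conclusion.** The point holds in a limited form. As stated, the same-arm rule together with person-by-person entry leaves some participants without concealed allocation, and nothing in the article prevents this. It concerns only partners and first-degree relatives who enter after a family member has been randomised.

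The size of any bias cannot be computed, because the number of such relatives and what they or the staff know are not given. If late joiners are few it is probably small: about 2-10% of the 0.107 target for a 2-10% share and a shift of 0.107. Those figures assume equal shares of late joiners in both arms and a selection shift as large as the target effect. A smaller shift lowers them in proportion, and a larger one raises them. This is an inexpensive improvement and no threat to the trial as a whole.

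**What to change.** Keep the same-arm rule and make three additions.

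1. At the prescreening call, ask whether a partner or first-degree relative is taking part or intends to. Where such people are already known and willing, complete consent, screening and baseline measurements for all of them, then randomise the family once, as a unit. There is no need to hold the first member back for relatives who might come forward later.
2. Record family links and the order of enrolment.
3. Prespecify a sensitivity analysis of the primary outcome limited to the first-randomised (index) member of each family, keeping whole any family randomised together as a unit. All of these people had a concealed allocation, so the restriction preserves the randomised comparison. Late joiners remain in the primary analysis.

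If recruitment has already closed, items 2 and 3 can still be done, provided that family links and enrolment order can be recovered. If the full protocol already sets the order of family enrolment, one sentence saying so covers item 1.

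The cost is a short delay for some families, one extra data flag, and slightly lower precision in the sensitivity analysis.

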### Safety considerations

Use of the mHealth intervention is not expected to be associated with health risks beyond those typically experienced by individuals leading an active lifestyle. Considering the low risk, no Data Safety Monitoring Board or Safety Committee will be installed. Multiple measures will be taken to reduce any potential safety risk. First, it will be explicitly communicated that the MIND-PRO app does not replace any regular primary or secondary care. Second, if any condition requiring medical attention arises during the study (eg, hypertension that qualifies for treatment according to clinical guidelines, as observed during the measurements at the screening visit), participants will be referred to their own doctor by the assessor, coach or the study investigator. Third, adverse events will be checked using a questionnaire at 6 months, for which participants will receive notifications on their smartphone and reminders through email. Fourth, the MIND-PRO app is built in accordance with the highest security requirements in healthcare and complies with NEN 7510, the Health Insurance Portability and Accountability Act and General Data Protection Regulation (GDPR).

## Statistical analysis and quality assurance

### Sample size

The sample size was calculated based on the expected effect of the intervention on our primary effectiveness outcome in individuals with low education, used as a proxy for low SES, from our previous prevention trials. In participants with a low educational level in the HATICE trial,^16^ the mean difference between intervention and control participants in change from baseline was 0.107 (pooled SD 0.454) for the composite z-score after 1.5 years. In the preDIVA trial,^30^ the difference in composite z-score between individuals with a low educational level who developed dementia and those who did not during 6–8 years of intervention was 0.096 after 24 months. Therefore, a mean difference in change of 0.107 was considered as potentially clinically relevant with respect to the risk of dementia. For the effect of the intervention within specific migrant groups, no data are available. With 277 participants per treatment arm, we will have 80% power (with alpha set at 0.05) to detect a 0.107 (pooled SD 0.454) difference on our primary effectiveness outcome. To adjust for an anticipated drop-out of 20% in this specific target population, 692 participants will be recruited.

### Data analysis

The primary effectiveness outcome is the difference between the composite z-score after 12 months and the baseline composite z-score ((z_SBP_+z_non-HDL cholesterol_+z_BMI_)/3). The baseline mean and SD will be used to calculate composite z-scores at both time points to be able to detect a change. For the primary analyses, we will use a linear mixed effects model with individual observations nested within ethnic groups, operationalised by a random intercept and/or slope (depending on best model fit). If needed, we will explore the impact of any baseline imbalances by including imbalanced factors as a covariate in a sensitivity analysis. A per-protocol analysis will be done, based on uptake within the first month and continued use during the whole intervention period. Exploratory subgroup analyses on the primary outcome will be performed for ethnic group, sex, age group, history of CVD and diabetes.

We will conduct a sensitivity analysis using multiple imputation for the primary effectiveness outcome. Implementation of the intervention will be analysed with a series of implementation outcomes, as summarised in table 2. We will investigate frequency of app use and contact with the coach in relation to the effect on the primary outcome. We will graphically portray the Likert scales for the questionnaires and perform thematic analysis for the in-depth interviews. The interview guides can be found in the online supplemental appendix 3.

For the secondary outcomes, the effect on the CAIDE dementia risk score and its individual components (ie, blood pressure, BMI, total cholesterol, physical activity) will be analysed using the same model as for the primary analysis. In addition, as an exploratory analysis, the effect on daily changes in general movement will be assessed based on the data collected with the BeHapp application.^28 31 32^ For that purpose, time series analysis will be performed to detect trends in this longitudinal data as a function of intervention, accounting for clustering within ethnicities.

Scales for disability, depressive symptoms and cognitive functioning, mostly ordinal, will also be analysed as linear scales if the data characteristics allow. The same model as used for the primary analysis will be employed. Poisson regression or zero-inflated models may be applied to distributions resembling count or zero-inflated data. A description of the cost-effectiveness analysis can be found in online supplemental appendix 1.

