	Sustainability	Adherence	Coaches	After 6 months

* We used several questions from the validated mHealth App Usability Questionnaire for Interactive mHealth Aapps (MAUQ) (), where applicable to our intervention.^38^

† 30 participants (10 Dutch, 10 Turkish, 10 South-Asian Surinamese) will be invited for an interview on the implementation outcomes.

mHealthMobile Healthn.a.not available

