## Discussion

The rationale for our target group, individuals aged 50–75 years of low SES and/or migration background with elevated dementia risk factors or CVD, is twofold. First, most dementia risk factors exert their strongest detrimental effect in midlife, therefore optimising these risk factors in (late) midlife, rather than late-life is likely to be more effective for the prevention of cognitive decline and old-age dementia.^33 34^ Second, as the prevalence of dementia in high-income countries is higher among people of low SES and/or migration background, there is more room for reducing dementia risk factors in these populations.^35 36^

Recruiting participants from the HELIUS cohort has its advantages, such as feasibility, but it also introduces potential selection bias. Although demographic differences between the baseline population and the general population were limited,^19^ these differences may have widened over time and participants may be healthier and more motivated to change their lifestyles, a common challenge in preventive studies that complicates generalisability. Additionally, by narrowing our focus to three specific ethnic groups, we acknowledge that the findings of this study may not be applicable to other ethnic populations. However, this approach was chosen for practical feasibility, enabling us to focus on groups with the highest risk of dementia, based on measured risk factors within the HELIUS study.

Furthermore, in the proposed study design, we chose ethnically matched lifestyle coaches because they are likely more attuned to the preferences and needs within their cultural context. This approach mirrors common practices in Dutch primary care, where GPs often employ ethnically matched nurses to enhance the acceptability and perceived appropriateness of lifestyle guidance in cardiovascular risk management.^37^

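### The primary model treats three deliberately chosen ethnic groups as a random factor and lets model fit decide on a random slope, so the target and standard error of the primary test are not fixed in advance

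*Protocol article*

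**What the plan says.** The primary outcome gives one number per participant: "The primary effectiveness outcome is the difference between the composite z-score after 12 months and the baseline composite z-score" (Data analysis). The primary model is a linear mixed model with "individual observations nested within ethnic groups, operationalised by a random intercept and/or slope (depending on best model fit"). The section does not say which variable the slope is on, which fit criterion decides, or how degrees of freedom are obtained. It carries the same model to the CAIDE score and its components, and to the disability, depression and cognition scales where their distribution allows. It also plans an exploratory subgroup analysis by ethnic group.

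Ethnicity has three levels. Table 2 names them in its interview footnote ("30 participants (10 Dutch, 10 Turkish, 10 South-Asian Surinamese"), and the Discussion describes the choice as made "by narrowing our focus to three specific ethnic groups", adding that the findings may not carry over to other ethnic populations. Allocation is "using a computer algorithm in a 1:1 manner, stratified by ethnicity" (Randomisation and blinding).

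The Sample size section plans 277 per arm "to detect a 0.107 (pooled SD 0.454) difference on our primary effectiveness outcome", stating that "we will have 80% power (with alpha set at 0.05"). It has no term for variation of the effect between ethnic groups, and it says that no data on the effect exist for specific migrant groups.

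**The concern.** A random factor suits levels that stand for a wider population and are numerous enough to estimate a variance. Neither holds here. The three groups were picked deliberately, the authors do not claim to generalise beyond them, and three levels leave 2 degrees of freedom for a between-group variance.

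The random intercept does little harm, because the treatment contrast is made within ethnic groups. The slope is different. A random treatment slope adds the spread of three ethnic-specific effects to the standard error and changes the question to the average effect over hypothetical ethnicities. The plan leaves the choice between these models to the trial data. The primary confidence interval and p-value therefore depend on a selection step driven by a poorly estimated variance, while the sample size was computed for a plain two-group comparison.

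**Working it through.** **Inputs.** From Sample size: difference 0.107, SD 0.454, 277 per arm (554 completers), alpha 0.05, 80% power. From Discussion and Table 2: three groups. Assumed: two-sided test, equal thirds, slope on treatment, one extra variance parameter when the slope is added, AIC as the fit criterion, Wald z-test.

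**1. The plan's own figure.** n per arm = 2 × [0.454 × (1.960 + 0.842) / 0.107]² ≈ 283, against 277 stated, a 2% gap. With 277 per arm, SE = 0.454 × √(2/277) = 0.0386, 0.107/0.0386 = 2.77, and power is 79.2%. For recruitment, 2 × 277 / 0.80 = 692.5, against 692. The stated size is reproduced as a plain two-group comparison.

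**2. Ethnicity fixed, or random intercept only.** The treatment effect is estimated within groups on about 550 residual degrees of freedom. Power stays at 79%.

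**3. Random treatment slope.** Each ethnic-specific effect has variance v = 4 × 0.454² / (554/3) = 0.00446, SE 0.067. Let s² be the sample variance of the three estimated effects (2 df). REML gives a slope variance of max(0, s² − v), and the SE of the average effect is √(max(v, s²)/3). With no true heterogeneity, the slope variance is still estimated above zero with probability exp(−1) = 37%, which shows how noisy it is.

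**4. What selection by fit does.** Write r = s²/v. For r > 1, adding the slope raises twice the REML log-likelihood by 2(r − 1 − ln r). AIC keeps the slope when this exceeds 2, that is, when r > 3.15. With no heterogeneity the probability is exp(−3.15) = 4.3%. Once the slope is kept, the SE is at least √3.15 = 1.77 times larger: 0.0386 × 1.77 = 0.068. An estimate exactly equal to the planned 0.107 then gives z of at most 0.107/0.068 = 1.57, short of 1.96. Keeping the slope thus usually decides the primary result.

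**5. Simulated power under this rule** (average effect 0.107 throughout):

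| Effects in the three groups | Slope kept by AIC | Power, ethnicity fixed | Power after selection |
|---|---|---|---|
| 0.107 / 0.107 / 0.107 | 4% | 79% | 76% |
| 0.157 / 0.107 / 0.057 | 13% | 79% | 70% |
| 0.207 / 0.107 / 0.007 | 43% | 79% | 49% |

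With a mixture likelihood-ratio test instead of AIC, the first and third rows become about 77% and 53%.

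**The case against.** **The slope may rarely be kept.** If the effect is the same in every group, AIC keeps it in about 4% of trials and power falls only from 79% to 76%. This stands. The larger losses need heterogeneity that the protocol neither documents nor excludes.

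**The slope is undefined.** If baseline and 12-month values were modelled as repeated observations, the slope could be on time, and the power figures would apply only to a slope involving treatment. This also stands. The treatment reading is natural for a single change score but not certain. On either reading, the three-level random factor and the choice by fit remain.

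**Details belong in an analysis plan.** This is true of the fit criterion and the degrees-of-freedom method. It is not true of the rule itself, which the article states: ethnicity is random, and fit chooses the structure.

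**Two stronger readings are tempting but not supported.** A reader might infer that the primary test will rest on 2 degrees of freedom with almost no power. Always fitting the slope and always using t on 2 df does give about 4% power. But the protocol fits the slope only if fit favours it and names no such reference distribution. Using 2 df only when the slope variance is positive already gives about 50%. Under AIC selection, with 2 df only when the slope is kept, power is 76% for a homogeneous effect.

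A reader might also infer inflated type I error, since a random-slope z-test rejects about 7.4% when effects vary with SD 0.05 around a population mean of zero. That null concerns a population of ethnicities, and under it the fixed model rejects 11.7%. For the average effect in these three groups, the slope test is conservative (2.9% with effects +0.05/0/−0.05) and the fixed test holds 5%.

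**Conclusion.** The concern holds as one about an unfixed primary model. The random structure, and with it the target and standard error of the primary test, is left to the data over three levels that the authors chose and do not generalise from. The cost in power runs from about 3 percentage points with equal effects to about 9 with effects 0.157/0.107/0.057 and about 30 with 0.207/0.107/0.007. These sizes rest on 554 completers in equal thirds, SD 0.454, a treatment slope, AIC and a Wald z-test. The unequal effects are illustrations, not forecasts. If only an intercept is retained, the planned power is essentially intact. No type I error problem is claimed for the average effect in these three groups. This should be fixed before analysis; it does not invalidate the design or the sample size.

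**What to change.** State one primary model in advance: the change in composite z-score on treatment arm, with ethnicity as a fixed three-level covariate (the randomisation stratum), a single common treatment effect, no random slope for ethnicity and no choice by fit. Examine treatment by ethnicity only in the exploratory subgroup analysis already planned. Use the same specification for every outcome that is to follow the primary model.

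The cost is a sentence or two in the protocol or analysis plan. No new data or extra participants are needed, and the stated sample size keeps its 79% power. Compared with an intercept-only mixed model, the estimate is practically unchanged. The conclusion is limited to these three ethnic groups, a limit that the Discussion already accepts.

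### The primary change-score model names no baseline covariate, and adjustment is left to a sensitivity analysis triggered by observed imbalance, which costs precision and leaves chance baseline imbalance in the estimate

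*Protocol article*

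**What the plan says.** All of this is in the Protocol article.

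- **Outcome (Data analysis):** "The primary effectiveness outcome is the difference between the composite z-score after 12 months and the baseline composite z-score". On scaling: "The baseline mean and SD will be used to calculate composite z-scores at both time points to be able to detect a change". Each component therefore has SD 1 at baseline.
- **Model (Data analysis):** "we will use a linear mixed effects model with individual observations nested within ethnic groups", with a random intercept and/or slope chosen by fit. No baseline covariate is named.
- **Covariates (Data analysis):** "If needed, we will explore the impact of any baseline imbalances by including imbalanced factors as a covariate in a sensitivity analysis".
- **Reach:** the same section applies the primary model to the CAIDE score and its components. It also applies it to the disability, depression and cognition scales where these are treated as linear.
- **Allocation (Randomisation and blinding):** "Randomisation will take place in the app using a computer algorithm in a 1:1 manner, stratified by ethnicity". The baseline composite is not a stratification factor.
- **Sizing (Sample size):** the target is the HATICE low-education result, where the mean difference in "change from baseline was 0.107 (pooled SD 0.454) for the composite z-score after 1.5 years".

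**The concern.** An unadjusted change score fixes the slope of the 12-month value on baseline at 1. If the true slope is lower, participants who start high tend to fall more in both arms. Two things follow.

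1. Part of the variance of the change is predictable from baseline, and the comparison of arms carries it as noise.
2. If the arms differ by chance at baseline, part of that difference passes into the estimated effect.

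The imbalance rule does not deal with either. It selects covariates by how unequal they look, whereas what matters is how well they predict the outcome. The strongest predictor available, the baseline value of the outcome itself, is known in advance and already collected. Under the rule it would enter only if judged imbalanced, no threshold is given, and the headline estimate would still be the unadjusted one. Readers could then face two estimates with no stated rule for which to rely on.

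**Working it through.** **Inputs from the Sample size section:** difference 0.107, SD of change 0.454, 277 per arm, 80% power, alpha 0.05 (taken as two-sided), 20% drop-out, 692 recruited.

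**Assumed, because the article does not give them:** pairwise correlation r among the three standardised components of 0 to 0.3, and equal composite variance at both visits. The second assumption is relaxed in step 5. Participants are treated as independent.

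**1. The plan's own figure.** n per arm = 2 × (1.960 + 0.842)² × 0.454² / 0.107² = 282.6, so 283 against the stated 277 (2.2% apart). Power at 277 per arm is 79.2% by the normal approximation and 79.1% by the t distribution. 554 / 0.80 = 692.5 against 692. The sizing reproduces and matches an unadjusted change-score analysis.

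**2. Implied baseline SD and correlation.** Baseline composite variance = (1 + 2r)/3. With equal variances, rho = 1 − 0.454² / (2 × variance).

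**3. Precision.** Residual variance with baseline as covariate, divided by the variance of the change score, is (1 + rho)/2. Power below is t-based at 277 per arm.

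| r | Baseline SD | rho | Variance ratio | Residual SD | Power |
|---|---|---|---|---|---|
| 0 | 0.577 | 0.691 | 0.845 | 0.417 | 85.3% |
| 0.1 | 0.632 | 0.742 | 0.871 | 0.424 | 84.3% |
| 0.2 | 0.683 | 0.779 | 0.890 | 0.428 | 83.5% |
| 0.3 | 0.730 | 0.807 | 0.903 | 0.432 | 83.0% |

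The gain equals that from 11% (1/0.903) to 18% (1/0.845) more participants.

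**4. Chance imbalance.** SE of the baseline difference = baseline SD × √(2/277). The shift in the change-score estimate is (1 − rho) × the baseline difference.

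- r = 0: SE = 0.577 × 0.0850 = 0.0491. At 1.96 SE the shift is 0.309 × 1.96 × 0.0491 = 0.030, and 0.0297/0.107 = 28%.
- r = 0.3: SE = 0.730 × 0.0850 = 0.0621. At 1.96 SE the shift is 0.193 × 1.96 × 0.0621 = 0.024, and 0.0235/0.107 = 22%.
- At 1 SE the shift is 0.012 to 0.015, or 11 to 14% of the target.

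**5. Unequal variances.** Let k be the 12-month SD divided by the baseline SD, v0 the baseline variance and v1 = k² × v0. Then rho = (v0 + v1 − 0.454²) / (2√(v0·v1)), the residual variance is v1(1 − rho²), and the slope on baseline is k × rho.

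| k | Variance ratio | Power | Shift at 1.96 SE | Share of 0.107 |
|---|---|---|---|---|
| 0.9 | 0.74–0.79 | 88–90% | 0.035–0.039 | 33–36% |
| 1.0 | 0.85–0.90 | 83–85% | 0.024–0.030 | 22–28% |
| 1.1 | 0.93–0.98 | 80–82% | 0.011–0.020 | 10–18% |

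**The case against.** The strongest reply is that the article lists no fixed effects at all. Even the treatment term is not written out, so the absence of a baseline term is inferred, and a fuller analysis plan may include one. This stands as a limit: a reader might infer that the baseline composite has been positively excluded, and the text does not say so. But the article does more than stay silent. It gives covariate adjustment a place, and that place is a conditional sensitivity analysis.

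Other stronger readings are tempting and are not supported:

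- **That the primary estimate is biased.** Under 1:1 randomisation a change-score comparison is unbiased over randomisations. What is lost is precision, together with accuracy conditional on the imbalance that actually occurs.
- **That observed imbalance decides the primary result.** The data-dependent step is confined to a sensitivity analysis.
- **That selecting people for raised risk factors at the screening measurement produces the regression to the mean.** Under Study population and recruitment and Study procedures, candidates are identified largely from earlier HELIUS data, and the baseline components are measured later. Entry can also rest on smoking, depression, diabetes, inactivity or cardiovascular disease, none of which is in the composite. In the calculation, a slope below 1 comes from an imperfect correlation between visits under the assumed variances.
- **That the trial is underpowered and adjustment rescues it.** 79% against 80% is a trivial gap.

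The size of the gain is also open to challenge, since the article gives neither the correlation nor the 12-month variance. That stands too: with a 12-month SD 10% above baseline, the gain is only about 1 to 3 points.

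**Conclusion.** The point holds as one of efficiency and conditional accuracy, and it is worth acting on. As described, the primary analysis is an unadjusted change-score comparison, with covariates admitted only in a secondary model and only after imbalance has been seen. The two costs are a few points of power, and exposure of the headline estimate to a chance baseline difference that could amount to a fifth to a quarter or so of the target effect at 1.96 SE. Both figures rest on assumed component correlations of 0 to 0.3 and equal variances. Across a 10% change in the 12-month SD either way, power with adjustment runs from about 80% to 90%, and the shift from about 10% to 36% of the target. In large samples, adjusting for baseline does not lose precision against the change score, so uncertainty about the size of the gain is no argument against adjusting.

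**What to change.** State in the analysis plan that the primary model includes the baseline composite z-score as a pre-specified fixed covariate, with ethnicity as the stratification factor. The definition of the outcome can stay: once baseline is in the model, the treatment coefficient is the same for the change and for the 12-month value. Do the same for each linear-scale secondary outcome, using its own baseline value. Drop the imbalance trigger. If a further adjusted model is wanted, name its covariates in advance, for example age and sex, and report it as supportive whatever the baseline table shows. If the full plan already contains the baseline term, a sentence saying so is enough.

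The cost is one or two sentences before outcome data are analysed. The baseline values are already collected, and the sample size need not change.
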